##### Participation of the healthy controls

2.3.1.2

Participants who will meet the following criteria will be included:1.Age of 19 to 35 years.2.BMI of 18.5 to 23 kg/m^2^.3.No evidence of acne.4.(Only for women) regular menstrual cycle during the last 3 months.5.No digestive-related uncomfortable symptoms in usual situations.6.No abdominal muscle tension.7.Other disorders that may affect the outcomes.8.Voluntary participation in this clinical trial.

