#### Questionnaire

2.5.1

The participants will complete a questionnaire that would include general sociodemographic information (e.g., age and sex), personal habits (e.g., smoking, alcohol consumption, sleep pattern, and dietary habits),^[4,13]^ anthropometric measurements (e.g., height, weight, and BMI), pregnancy, menstrual pattern and history, use of oral contraceptives, history of adolescence acne, history of acne in relatives, relevant comorbidities (e.g., polycystic ovary syndrome, hirsutism, type II diabetes, and thyroid disease), acne pattern identification,^[14]^ and stress level during the last month, which will be self-assessed in accordance with the stress response inventory.^[15]^

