### Statistical methods

2.8

Data will be displayed as means ± standard deviations for continuous data or n (%) for categorical data. Statistical analyses will be conducted with a 95% confidence interval using the SPSS 21.0 (IBM SPSS Statistics, New York, NY). An independent *t* test will be performed for the comparison of specific biomarkers associated with the pathogenesis of acne by analyzing metabolomics/molecular biomarkers and skin biophysical parameters between the healthy subjects and participants with acne vulgaris. One-way analysis of variance will be performed for the comparison of the differences in these biomarkers among 3 groups (mild, Gr 1-2; moderate, Gr 3-4; severe, Gr 5-6), which we will classify in accordance with the severity of acne using the KAGS. The correlation between the biomarkers and various factors, such as acne symptoms, dietary habit, stress level, sleep pattern, and menstrual pattern, will be examined using the Pearson correlation test. The mean value of a variable will be used in place of the missing data value for that same variable.

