## Discussion

3

Although accumulating evidence underlines the role of Western diet, stress, and smoking in the pathogenesis of acne, the pathogenesis and aggravating factors of acne are not yet fully elucidated. Therefore, the metabolomics/molecular biomarkers could be an issue when discussing acne management with patients.

This will be the first protocol that would discover new diagnostic biomarkers in acne by analyzing metabolomics/molecular biomarkers and skin biophysical parameters between healthy individuals and patients with acne, compare the differences in these biomarkers according to the severity of acne, and explore the correlation between these biomarkers and various factors. In this study, we will analyze the molecular biomarkers, including zinc, calcium, and ROS, as well as existing known inflammatory cytokines and chemokines, and targeted and untargeted metabolite biomarkers, such as steroidal hormones, fatty acids, and endogenous small metabolites closely related to energy metabolism and lipid/steroid biosynthesis in terms of systems biology. We will also use the skin biophysical measurement devices Sebumeter SM815, Skin-Thermometer ST500, and Reviscometer RVM600 and questionnaires that would include general sociodemographic information, personal habits, anthropometric measurements, pregnancy, menstrual pattern and history, use of oral contraceptives, history of adolescence acne, history of acne in relatives, relevant comorbidities, acne pattern identification, and stress level.

Several methodological limitations within this study warrant further discussion. First, only young adults will be studied, and the sample size was decided in accordance with the size of the metabolite kit with expert opinions in metabolomics, molecular biology, dermatology, and statistics and not a power analysis. Second, diet tracking will not be performed. Third, this study has a cross-sectional design; because of the nature of this study design, interpretations of the results will be limited.

Despite these limitations, this study could be helpful in providing new diagnostic human biomarkers in acne and correlation between human biomarkers and patterns of acne. The findings of this trial may have important implications for the new approach of personal individualized therapy by identifying and differentiating the treatment methods of acne according to the biological and metabolic biomarkers based on human blood samples and patterns of acne.

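### Pearson correlation is the only method for every lifestyle factor; where an item has three or more unordered categories, the result depends on how the answers are numbered

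*Protocol article*

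**What the plan says.** Section 2.8 (Statistical methods) gives one method for relating biomarkers to the other factors, which are "such as acne symptoms, dietary habit, stress level, sleep pattern, and menstrual pattern, will be examined using the Pearson correlation test". It states no alternative and no coding rule. The same section recognises categorical variables for description, as "n (%) for categorical data", and uses one-way analysis of variance to compare the three acne severity groups. It does not extend a group comparison to the questionnaire factors.

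Section 2.5.1 (Questionnaire) shows where the factors come from:
- Sleep and diet are among the "personal habits (e.g., smoking, alcohol consumption, sleep pattern, and dietary habits".
- Menstruation is listed with "pregnancy, menstrual pattern and history, use of oral contraceptives".
- Stress is the only one of these lifestyle factors tied to a named instrument, "which will be self-assessed in accordance with the stress response inventory".

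The Discussion adds that "diet tracking will not be performed". Section 2.3.1.2 requires healthy women to have had regular cycles over the last three months. Section 2.3.1.1 sets no such condition for women with acne.

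**The concern.** Pearson's r measures a straight-line relation between two numerical variables. Items described as habits or patterns, with no score named, may well be recorded as types. If a type has three or more unordered levels, the numbers given to the levels are arbitrary, and so is the coefficient. Two analysts with the same data could report a positive, a negative or a null association. Even for ordered answers, a straight-line measure misses a U-shaped relation, such as short and long sleepers both differing from the rest.

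The correlation of biomarkers with lifestyle factors is a stated objective in the Introduction and in section 2.1. In a discovery study its use is to decide which associations to follow up. A coding-driven null could drop a real candidate, and a coding-driven sign could misdirect later work.

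**Working it through.** The plan gives no power, effect size or target correlation for this aim, so there is no figure to reproduce. The check asks how much the coding alone can change the result.

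**Inputs from the protocol.** Section 2.7 plans 100 participants: 40 healthy (20 women) and 60 with acne (30 women). That gives 20 + 30 = 50 women for menstrual pattern. Section 2.8 says "Statistical analyses will be conducted with a 95% confidence interval"; a two-sided 5% test is assumed from this.

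**Assumptions, not in the protocol.** Three unordered categories of equal size, biomarker means (0, 0.8, 0), SD 1 within each category.

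**Step 1: population correlation by coding.** The formula is r = cov(code, mean) / √[var(code) × (1 + var(mean))].
- Average of the means = 0.8/3 = 0.267; var(mean) = 0.64/3 − 0.267² = 0.142.
- Any assignment of 1, 2, 3 has average 2 and variance 2/3. The denominator is √(0.667 × 1.142) = 0.873.
- Raised category coded 2: cov = 1.6/3 − 2 × 0.267 = 0, so r = 0.
- Raised category coded 3: cov = 2.4/3 − 0.533 = 0.267, so r = 0.267/0.873 = +0.31.
- Raised category coded 1: cov = 0.8/3 − 0.533 = −0.267, so r = −0.31.
- Coding-free measure: eta = √(0.142/1.142) = 0.35.

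With a shift of 0.5 SD, r is 0 or ±0.20 (eta 0.23). With 1.0 SD it is 0 or ±0.37 (eta 0.43).

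**Step 2: power (simulation, 20,000 data sets per row, shift 0.8 SD).**

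| N | Category means (ANOVA) | Pearson, raised category at an end code | Pearson, raised category at the middle code |
|---|---|---|---|
| 50 | 64% | 62% | 4% |
| 60 | 73% | 69% | 4% |
| 100 | 92% | 89% | 4% |

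The ANOVA column can be checked with the noncentral F distribution. At N = 50 with 17 in the raised category, the grand mean is 17 × 0.8/50 = 0.272 and the noncentrality is 17 × 0.528² + 33 × 0.272² = 7.18. The critical F(2, 47) is 3.20, so power is 64%. At N = 100 with 33 in the raised category, the noncentrality is 33 × 0.536² + 67 × 0.264² = 14.15. The critical F(2, 97) is 3.09, so power is 92%.

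Under the middle coding a larger sample does not help, because the population correlation is zero.

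**Step 3: where Pearson does no harm.**
- Binary item: t = r√[(n − 2)/(1 − r²)] is the two-sample t statistic. In a generated example the two p-values agreed (0.00047), and recoding did not change them.
- Ordered item with a linear trend (0, 0.4, 0.8 SD): across repeated runs Pearson had 61 to 63% power against 50 to 52% for ANOVA at N = 50, and 90% against 83 to 84% at N = 100.

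**Step 4: would a rank method cure the U shape?** With the middle of three ordered groups 0.8 SD higher, Spearman also has about 4% power. It does not.

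**Step 5: menstrual pattern.** Healthy women make up 20/50 = 40% of the women. If the item records regularity, they are all in the regular category by eligibility. Three equal categories in the pooled women are then implausible, so the N = 50 row is only an illustration. In addition, a pooled association would be partly mixed with acne status.

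**The case against.** The strongest reply is that the protocol never says these items are categorical. Sleep could be recorded in hours, menstruation as cycle length in days and diet as a frequency score. The questionnaire is not reproduced, and an article commonly leaves item scales to the full protocol. This stands, and it makes the harm conditional. It does not remove the point, because the method is stated in the text for all factors alike and is not left open.

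It is also fair that 4% is the worst case. With the raised category at an end code the loss is only 2 to 4 percentage points, nothing is lost for binary items, and Pearson is better for a linear trend.

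A reader might infer that the whole correlation aim is unsound. The documents do not support that. The aim also covers stress, which has an inventory, and acne symptoms, for which section 2.5.2 provides lesion counts. Nor does any passage say that a null correlation will be reported as absence of a relation. Finally, section 2.7 describes the study as preliminary and exploratory. That excuses low power, but not a coefficient whose value depends on arbitrary numbering.

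**Conclusion.** The point holds in conditional form. Section 2.8 fixes Pearson for a mixed list of factors, three of which have no named score. For any of these with three or more unordered levels, the size, sign and significance of r depend on coding. Under the assumed three equal categories and 0.8 SD shift, the same real difference is detected in about 4% or 62% of studies at N = 50, and in about 4% or 89% at N = 100. Comparing category means gives 64% and 92% whatever the coding. These figures rest on assumptions about category number, balance and effect size that the protocol does not give. There is no harm for binary items or for roughly linear scores. The consequence is confined to an exploratory aim; the comparison of healthy participants with acne patients is untouched.

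**What to change.** In section 2.8, state the recorded scale of each factor and match the method to it:
- **Quantitative scores** (the stress inventory total, or hours of sleep if so recorded): Pearson, where a roughly linear relation is expected.
- **Ordered answers with an expected monotone relation:** Spearman or a trend test.
- **Unordered factors, and ordered ones where a U shape is plausible, such as sleep:** compare biomarker means across categories, with the factor entered as categorical. Spearman and trend tests miss a U shape just as Pearson does.
- **Menstrual pattern:** women only, and either within the acne group or adjusted for acne status, because regular cycles are an entry condition for healthy women.

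This takes a few sentences and needs no new data or software. The cost is one degree of freedom per added category, and some power if the relation is in fact linear: about 11 percentage points at N = 50 and 6 to 7 at N = 100 in the linear example above.

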#### Exploring biomarker with biological profiling

2.5.5

The whole blood, which will be collected in serum tubes, will be allowed to clot by leaving it at room temperature for 30 minutes. The clot will be removed by centrifuging at 3000 rpm for 10 minutes. All the serum samples will be stored at –70°C until further analysis. The concentrations of the cytokines (interleukin [IL-1α], IL-1β, IL-12β, IL-15, IL-6, and tumor necrosis factor-α) and chemokines (monocyte chemoattractant protein-1 and IL-8) in the serum will be determined using a bead-based multiplex assay for luminex platform (R&D Systems, Minneapolis, MN) according to the manufacturer's instructions and measured using a Luminex 200 system (Luminex Corporation, Austin, TX). Each serum sample will be run in duplicates and averaged to calculate the concentrations. The Enzyme-Linked Immunosorbent Assay kits that will be used to analyze the serum calcium, zinc, and ROS will be purchased from Abcamb (Cambridge, UK). Each product will be used following the instructions provided by the manufacturer. The absorbance will be measured at 450 nm using the microplate reader (Versa Max) and analyzed using the SoftMax pro software (Molecular Devices).

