### Sample size

2.7

The current study is a preliminary cross-sectional trial with the aims of discovering novel specific biomarkers in acne by investigating metabolomics/molecular biomarkers between healthy individuals and patients with acne, comparing the differences in these biomarkers according to the severity of acne, and exploring the correlation between the biomarkers and acne symptoms. In other words, this study is, to the best of our knowledge, the first of its kind and not intended to validate affirmatively the effects of certain interventions on acne, but rather to compare the biomarkers of patients with acne with those of healthy individuals. If the aims of the pilot study do not include any hypothesis tests, the power level of a test procedure is not a valid consideration for sample size.^[20]^ Moreover, in the metabolomics study design, a sample size of 3 to 5 per group may give useful preliminary data that can be used to design more elaborate and/or targeted metabolomics studies and the number of sample size for a metabolomics experiment depends on the biological variability associated with the system being studied compared with the analytical variability of the analytical system.^[21]^ Therefore, in this exploratory study, the number of patients to be included will be set to 40 healthy subjects (20 men and 20 women) and 60 patients with acne (30 men and 30 women) which enables the assessment of the difference in metabolomics/molecular biomarkers between healthy individuals and patients with acne including a respective 95% confidence interval, with sufficient precision according to the size of the metabolite kit with expert opinions in metabolomics, molecular biology, dermatology, and statistics.

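### Filling every missing value with the variable's mean either shrinks the acne-control difference or understates its standard error, depending on which mean is meant

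*Protocol article*

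**What the plan says.** Statistical methods (2.8) gives a single rule for missing data: "The mean value of a variable will be used in place of the missing data value for that same variable". The article nowhere limits the missing fraction, says whether the mean is taken over everyone or within a group, or exempts any variable.

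The completed data feed three analyses in the same section:
- acne against healthy: "An independent *t* test will be performed for the comparison of specific biomarkers associated with the pathogenesis of acne";
- severity: "One-way analysis of variance will be performed for the comparison of the differences in these biomarkers among 3 groups";
- associations with lifestyle and symptom factors, which "will be examined using the Pearson correlation test".

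Intervals are part of the plan: "Statistical analyses will be conducted with a 95% confidence interval using the SPSS 21.0". Sample size (2.7) sets "40 healthy subjects (20 men and 20 women) and 60 patients with acne (30 men and 30 women") and justifies the number by the group difference, "including a respective 95% confidence interval, with sufficient precision according to the size of the metabolite kit".

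The cytokine and chemokine concentrations "in the serum will be determined using a bead-based multiplex assay for luminex platform" (2.5.5), and metabolites are measured by mass spectrometry (2.5.4). Neither section says how an undetected value is recorded.

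**The concern.** A filled-in mean carries no information about the participant, yet the t test, ANOVA and Pearson correlation count it as a measured value. What goes wrong depends on which mean is used. The overall mean moves each group towards the other. The group mean leaves the groups where they are but removes spread and adds false sample size.

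This matters because the sample size is defended by the precision of an interval for the group difference, and under either reading that interval is wrong: centred too close to zero, or too narrow. The article states this rule outright, so the problem is not a detail left to a fuller document.

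The assays raise a second, conditional worry. If an undetected concentration is stored as missing, the rule replaces a very low value with an average one.

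**Working it through.** The article gives no effect size, SD, power or missing rate, so there is no figure of the plan's own to reproduce.

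**Inputs from the article.** 40 healthy and 60 acne participants (2.7); pooled t test, Pearson correlation and 95% intervals (2.8).

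**Assumptions.** Two-sided 5% tests; missing fraction m of 5%, 10%, 20% or 30%, completely at random and equal in both groups; true difference 0.60 SD; true correlation 0.40. For orientation, with complete data the standard error is √(1/40 + 1/60) = 0.204 SD and the 95% half-width is 1.984 × 0.204 = 0.405 SD.

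**Overall mean.** Each filled group mean is (1−m) × its own mean + m × the overall mean, so the difference is multiplied by (1−m): 0.60 × 0.95, 0.90, 0.80, 0.70 = 0.57, 0.54, 0.48, 0.42. The reported standard error is also about (1−m) times the available-case one, so the t statistic hardly moves (at 20%: 0.480/0.183 = 2.62 against 0.602/0.228 = 2.64).

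**Group mean.** The SD is multiplied by about √(1−m), while n is overstated by 1/(1−m). The ratio of reported to true standard error is therefore about (1−m), and type I error is about 2[1 − Φ(1.96(1−m))]. At 20%: 2[1 − Φ(1.568)] = 11.7%.

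**Simulation, 20,000 data sets per cell:**

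| m | Rule | Estimate (true 0.60) | Reported SE | True SD of estimate | Coverage | Type I error | Power |
|---|---|---|---|---|---|---|---|
| 5% | overall | 0.569 | 0.199 | 0.199 | 0.949 | 0.054 | 0.809 |
| 5% | group | 0.600 | 0.198 | 0.208 | 0.938 | 0.063 | 0.840 |
| 5% | available cases | 0.599 | 0.209 | 0.208 | 0.954 | 0.050 | 0.809 |
| 10% | overall | 0.537 | 0.194 | 0.194 | 0.937 | 0.051 | 0.781 |
| 10% | group | 0.600 | 0.193 | 0.215 | 0.922 | 0.080 | 0.839 |
| 10% | available cases | 0.600 | 0.215 | 0.217 | 0.950 | 0.049 | 0.786 |
| 20% | overall | 0.480 | 0.183 | 0.185 | 0.896 | 0.051 | 0.736 |
| 20% | group | 0.599 | 0.182 | 0.229 | 0.883 | 0.119 | 0.850 |
| 20% | available cases | 0.602 | 0.228 | 0.229 | 0.950 | 0.048 | 0.736 |
| 30% | overall | 0.419 | 0.172 | 0.172 | 0.811 | 0.050 | 0.676 |
| 30% | group | 0.600 | 0.169 | 0.246 | 0.823 | 0.170 | 0.857 |
| 30% | available cases | 0.597 | 0.244 | 0.244 | 0.951 | 0.051 | 0.670 |

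The higher power in the group-mean rows comes from the inflated type I error.

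**Pearson, true r = 0.40, overall mean.**
- One variable incomplete: r is multiplied by about √(1−m). Simulated: 0.388, 0.376, 0.356, 0.333.
- Both incomplete, in different participants chosen independently: multiplied by about (1−m). Simulated with n = 100: 0.378, 0.357, 0.318, 0.278. With n = 60 and 20% missing, about 0.31.
- Both missing in the same participants: essentially no attenuation (about 0.39 to 0.40 at 20%).

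**Pearson, group mean, pooled sample.** Take a 1 SD group shift in both variables and no within-group correlation. The between-group variance is 0.4 × 0.6 × 1² = 0.24. Complete data give r = 0.24/1.24 = 0.19. With 20% filled in each variable, r = 0.24/(0.80 + 0.24) = 0.23. Here the rule raises the correlation.

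**Undetected values, only if coded as missing.** Assumed log-normal marker, log SD 1, log shift 0.6, overall-mean filling, raw-scale t test. The complete-data difference is e^1.1 − e^0.5 = 1.36 and power about 60% to 61%.

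| Undetected, controls / cases | Difference after filling | Power after filling |
|---|---|---|
| 20% / 7.5% | 1.04 | 38% |
| 30% / 13% | 0.91 | 28% |
| 40% / 20% | 0.77 | about 19% |
| 50% / 27% | 0.65 | 12% |

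In the 30%/13% case the filled value is about 2.98, although the limit is 0.59 and the true mean of those samples is 0.37. In the 40%/20% case, substituting half the detection limit on the same raw scale keeps power at about 60%.

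**The case against.** The study is declared preliminary and exploratory. It is cross-sectional with one 5 mL blood sample, so there is no follow-up attrition and missingness may be low. At 5% missing the effect is slight: 0.569 instead of 0.60 with coverage 0.949, or type I error of 6.3% on the group-mean reading. This stands, and it limits the severity.

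Some stronger readings are tempting but are not supported:
- **Inflated false positives in general.** The wording most plainly means the overall mean. On that reading type I error stays near 5% and power matches available cases; the harm is a shrunken estimate and lost coverage.
- **Correlations always attenuated.** This fails when both values are missing in the same people, and group-mean filling can push a pooled correlation up.
- **Undetected biomarkers will be given average values.** The article does not say that they are coded as missing. It refers to the manufacturer's instructions for the assays, and non-detect coding may sit in laboratory procedures. It also states no direction for any marker, so a claim that controls would be hit hardest is an assumption.
- **Mean filling against a log-scale analysis as the measure of damage.** In the 40%/20% example, half-limit substitution gives 79% power on the log scale but 60% on the raw scale. Only the raw-scale figure is like for like with 19%.
- **Menstrual pattern imputed for the 50 men.** Not applicable is not the same as missing, and the article does not say this would be done.

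What remains is that the stated rule is worse than plain available-case analysis under either reading, and nothing in the article softens it.

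**Conclusion.** The concern holds in a limited form. The rule is ambiguous, and both readings misstate the interval for the group difference. With the overall mean, the estimate is biased towards zero by about the missing fraction, and coverage drops to about 0.90 at 20% missing and 0.81 at 30%. With the group mean, the estimate is unbiased but type I error reaches about 12% and 17% at those fractions. Correlations may be weakened, unchanged or strengthened, depending on the missingness pattern and the mean used.

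These sizes rest on assumed missing fractions, missingness completely at random, and an assumed difference of 0.60 SD and correlation of 0.40. The below-detection loss additionally depends on undetected values being stored as missing and on a log-normal marker; it is an illustration, not a prediction.

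This is a should-fix. The study is exploratory and the harm may be small if little is missing, but the rule brings no benefit to set against it.

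**What to change.** In Statistical methods:
- Delete the mean-imputation sentence. Analyse available cases for each variable and report n by group.
- State that concentrations below detection are not treated as missing but as left-censored, for example a low-value substitution, with a rank-based or censored-data analysis when many are undetected (a substituted value is itself a single fill-in). Report detection rates by group.
- State that menstrual pattern is analysed in women only.
- Optionally, add multiple imputation, including group, sex and age, as a sensitivity analysis, since available-case results are themselves unbiased only if missingness is unrelated to the values.

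The cost is one paragraph of wording, with no change to participants, visits or assays. Some variables will have a smaller n and wider intervals: at 20% missing the standard error of the group difference is 0.228 SD, against 0.204 SD with complete data. That width is honest.
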